### **7.1.2 Serious Adverse Event**

A serious adverse event (SAE) is any experience that suggests a significant hazard, contraindication, side effect or precaution. It is any AE that results in any of the following outcomes:

- Death
- A life-threatening adverse event
- Inpatient hospitalization or prolongation of existing hospitalization
- A persistent or significant disability or incapacity
- A congenital anomaly/birth defect in the offspring of a subject who received the study treatment
- Important medical events that may not be immediately life-threatening or result in death or hospitalization but may jeopardize the subject or may require intervention to prevent one of the outcomes listed above. Examples of such events are intensive treatment in an emergency room or at home for allergic bronchospasm; blood dyscrasias or convulsions that do not result in hospitalization; or the development of drug dependency or drug abuse.

### **7.1.3 Unexpected Adverse Reaction**

An unexpected adverse reaction is an adverse reaction, the nature and severity of which is not consistent with the applicable product information (e.g., Investigator's Brochure for an unapproved

Protocol 15NRHC: A randomized, double-blind, placebo controlled parallel study investigating the effects of Niagen™ (Nicotinamide Riboside) on Niagen™ metabolites in healthy adults

investigational product or package insert/summary of product characteristics for an approved product).

#### **7.1.4 Laboratory Test Abnormalities**

The investigator must assess the clinical significance of all abnormal laboratory values as defined by the compendium of normal values for the reference laboratory. Specific laboratory parameters include, hemoglobin concentration, hematocrit, WBC count, RBC count, platelet count, neutrophil count, lymphocyte count, monocyte count, eosinophil count, basophil count, fasting glucose levels, creatinine concentration, glomerular filtration rate, Na+/K+ concentration, Cl concentration, total bilirubin, aspartate transaminase, alanine transaminase, and gamma-glutamyltransferase.

Any treatment emergent abnormal laboratory result which is clinically significant, i.e., meeting one or more of the following conditions, should be recorded as a single diagnosis on the AEs form in the study record:

- Accompanied by clinical symptoms
- Leading to interruption or discontinuation of the investigational product
- Requiring a change in concomitant therapy

This applies to any protocol and non-protocol specified laboratory result from tests performed after the first dose of the investigational product, which falls outside the laboratory reference range and meets the clinical significance criteria for liver and kidney tests as well as for hematology and clinical chemistry, etc. (i.e. AST and/or ALT > 2 x ULN).

This does not apply to any abnormal laboratory result which falls outside the laboratory reference range but which does not meet the clinical significance criteria or those which are a result of an AE which has already been reported.

Any laboratory result abnormality fulfilling the criteria for a serious adverse event (SAE) should be reported as such, in addition to being reported as an AE in the study record.

### **7.2 Treatment and Follow-up of AEs and Laboratory Abnormalities**

#### **7.2.1 Treatment and Follow-up of AEs**

AEs, especially those for which the relationship to the investigational product is suspected, should be followed up until they have returned to baseline status or stabilized.

If after follow-up, return to baseline status or stabilization cannot be established, an explanation should be recorded in the study record.

#### **7.2.2 Treatment and Follow-up of Laboratory Abnormalities**

In the event of subject-initiated withdrawal or clinically significant unexplained abnormal laboratory test values, the subject will be withdrawn from the treatment and will remain in the study and be required to attend all remaining study visits as part of a safety arm.

### **7.3 Reporting of SAEs and Unexpected Adverse Reactions**

The Qualified Investigator will be responsible for classification of an AE as an SAE within 24 hours of notification. Causality should be signed off by the Qualified Investigator prior to reporting to ethics and regulatory bodies. Notification of any serious adverse events must be made in writing to the study sponsor. The IRB will be notified of all SAEs and unexpected adverse reactions. All SAEs will be reported to the Therapeutics Products Directorate (TPD) in an expedited manner.

Protocol 15NRHC: A randomized, double-blind, placebo controlled parallel study investigating the effects of Niagen™ (Nicotinamide Riboside) on Niagen™ metabolites in healthy adults

The sponsor must notify the TPD of all serious adverse reactions as follows:

- a. If it is neither fatal or life threatening, within 15 calendar days after the day on which the sponsor becomes aware of the information; and
- b. If it is fatal or life threatening, must be reported as soon as possible, but not later than seven (7) days after the day on which the sponsor becomes aware of the information.

#### **7.4 Dietary monitoring**

Throughout the study, the subject's diet will be monitored via 3-day food diaries dispensed at each study visit; subjects will receive dietary counseling from a dietician and a weekly phone call from study staff. The 3-day food diary should list all foods ingested during 2 weekdays and 1 weekend day. In addition, the ingestion of all tryptophan- and niacin (nicotinic acid and nicotinamide)-rich foods should be listed in the 3-day food record.

### **8 STATISTICAL EVALUATION**

#### **8.1 Determination of sample size**

The planned sample size for this study is 140 subjects, with 35 subjects randomized to each treatment group. The primary efficacy endpoint is the change urinary methylnicotinamide levels from baseline to Day 56.

Power calculations were performed to determine the required sample size to provide 80% power at the 0.05 alpha level (that is, to have an 80% chance of obtaining  $p \leq 0.05$  significance).

The sample sizes assume that (1) the basal concentration SD is equal to the end-of-study SD for the placebo group, and (2) the correlation coefficient between baseline and end-of-study values is equal to 0.5.

Based on a previous study by KGK Synergize, the standard deviation of the urinary methylnicotinamide levels was estimated to be 3.1  $\mu\text{M}/\text{mM}$  Creatinine. With an estimated 20% attrition over the course of this study, 80% power and  $p \leq 0.05$  when comparing product to placebo, if the product produces at least a 2.5  $\mu\text{M}/\text{mM}$  Creatinine increase in urinary methylnicotinamide concentration, then a total of 128 subjects are required to be enrolled.

Based on a previous study by Fu et al. (1989), the standard deviation of the erythrocyte NAD levels was estimated to be 10.1  $\mu\text{M}$ . With an estimated 20% attrition over the course of this study, 80% power and  $p \leq 0.05$  when comparing product to placebo, if the product produces at least an 8.7  $\mu\text{M}$  increase in erythrocyte NAD levels, then a total of 140 subjects are required to be enrolled.

Because erythrocyte NAD levels are a secondary endpoint in this study and require a larger sample size, the study was powered on the erythrocyte NAD concentration.

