#### **Statistical tests:**

Numerical efficacy endpoints will be formally tested for significance between groups by Analysis of Covariance (ANCOVA). The dependent variable will be the value at each visit, the factor will be the treatment group, and the value at baseline (Day 0) will be the covariate. When the effect of treatment is significant ( $p\text{-value} \leq 0.05$ ), the pairwise Tukey-Kramer post-hoc test will be applied. Significant efficacy of the product, relative to placebo, will be inferred if the coefficient of the treatment group in the ANCOVA model is significantly different from zero ( $p \leq 0.05$ ). Numerical endpoints that are intractably non-normal will be assessed by the Mann-Whitney U test. A within group analysis on efficacy endpoints will be done using the Student's paired t-test or, in the case of intractable non-normality, the Wilcoxon sign rank test.

Probabilities  $\leq 0.05$  will be considered statistically significant. All statistical analysis will be completed using the R Statistical Software Package Version 3.2.1 (R Core Team, 2015) for Microsoft Windows.

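### Section 8.1: an 8.7 µM increase in erythrocyte NAD with SD 10.1 needs about 112–116 subjects, not 140, so the reason given for sizing the trial on NAD is reversed

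*Protocol*

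**What the plan says.** Section 8.1 sets out to find the sample size "to provide 80% power at the 0.05 alpha level". For both endpoints it assumes a correlation of 0.5 between baseline and end of study, 20% attrition, and a comparison of product with placebo.

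- **Urinary methylnicotinamide (primary):** SD 3.1 and increase 2.5 µM/mM creatinine; "then a total of 128 subjects are required to be enrolled".
- **Erythrocyte NAD (secondary):** "the standard deviation of the erythrocyte NAD levels was estimated to be 10.1" µM; "if the product produces at least an 8.7" µM "increase in erythrocyte NAD levels, then a total of 140 subjects are required to be enrolled".

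The section then concludes that erythrocyte NAD levels "are a secondary endpoint in this study and require a larger sample size, the study was powered on the erythrocyte NAD concentration". Sections 3 and 4 carry the 140 forward as planned enrolment, 35 per arm.

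Section 8.3 (Statistical tests) analyses the value at each visit by ANCOVA with baseline as covariate. If the treatment effect is significant, "the pairwise Tukey-Kramer post-hoc test will be applied". The same paragraph also infers efficacy against placebo if "the coefficient of the treatment group in the ANCOVA model is significantly different from zero" at p ≤ 0.05.

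**The concern.** The two calculations differ only in effect and SD. The endpoint with the larger effect relative to its SD should need fewer subjects, yet section 8.1 gives NAD more. Either an NAD input or the NAD total is wrong.

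This line is the only stated reason for enrolling 140 rather than 128. A reader cannot tell which NAD effect the trial was designed to detect, and the stated reason for preferring a secondary endpoint as the basis of sizing does not follow from the figures printed beside it.

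**Working it through.** **Inputs (section 8.1).** Alpha 0.05, power 80%, r = 0.5, attrition 20%, four equal arms. Sidedness is not stated; I take two-sided, because section 8.3 tests for a difference from zero. I assume equal SDs in the treated and placebo arms.

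**SD of change.** SD × √(2(1 − 0.5)) = SD, so the printed SDs apply directly to change from baseline.

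**Standardised effects.** Urine 2.5/3.1 = 0.806. NAD 8.7/10.1 = 0.861.

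**Reproducing 128 (urine).**
- Normal approximation: n = 2(1.960 + 0.842)²/0.806² = 24.14, so 25 per arm. Then 25/0.8 = 31.25, so 32 enrolled, and 32 × 4 = **128**.
- Noncentral t, rounding once: 25.13/0.8 = 31.4, so 32, and 32 × 4 = **128**.

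Both routes return the plan's own figure, so its method is identified.

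**Same routes for NAD.**
- Normal approximation: 2(2.802)²/0.861² = 21.16, so 22. Then 22/0.8 = 27.5, so 28, and 28 × 4 = **112**.
- Noncentral t, rounding once: 22.16/0.8 = 27.7, so 28, and 28 × 4 = **112**.
- Noncentral t, rounding at both stages: 23/0.8 = 28.75, so 29, and 29 × 4 = **116**. This route is the upper end; for urine it would give 26/0.8 = 32.5, so 33, and 132 rather than 128.

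The shortfall against 140 is (140 − 116)/140 = 17% to (140 − 112)/140 = 20%.

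**Other routes to 140 for NAD at 8.7/10.1.**

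| Variant | NAD total |
|---|---|
| One-sided | 84–88 |
| ANCOVA variance | 80–88 |
| Inflating by (1 + 0.2) | 108–112 |
| Mann-Whitney efficiency | 120–132 |
| Bonferroni for three comparisons | 140–152 |
| 90% power | 140–152 |

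The last two contradict the stated 0.05 or 80%, and they move urine to 160–172, not 128.

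**What would give 140.**
- Effect 7.7 µM: normal approximation 27.01, so 28, then 28/0.8 = 35, total 140. Noncentral t gives 35.002, which rounds up to 36 and 144.
- Effect 7.8 µM: noncentral t 34.14, so 35, total 140.
- SD 11.3 or 11.4 µM with 8.7 kept: noncentral t 34.35 or 34.93, so 35, total 140.

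**Power that 140 gives.** Completers per arm: 35 × 0.8 = 28. The noncentrality is the standardised effect × √(28/2). Under ANCOVA the residual SD is SD × √(1 − 0.5²) = 0.866 SD.
- Change score: urine 0.806 × 3.742 = 3.02; NAD 0.861 × 3.742 = 3.22.
- ANCOVA: urine 3.02/0.866 = 3.48; NAD 3.22/0.866 = 3.72.

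The critical value is about 2.0 unadjusted and about 2.61 for Tukey-Kramer with four groups (studentised range divided by √2).

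| Test, 28 per arm | Urine 2.5 | NAD 8.7 |
|---|---|---|
| Change score, unadjusted (as sized) | 84–85% | 89% |
| ANCOVA, Tukey-Kramer | 81% | 86% |
| ANCOVA, unadjusted coefficient | 93% | 96% |

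**The case against.** **The error is on the safe side.** It makes the trial larger than its NAD inputs require, and 140 covers the 128 for the primary endpoint. This stands, and it is why enrolment need not change. It does not make the printed figure or its rationale correct.

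**The ordering argument assumes equal SDs.** Section 8.1 equates baseline and end-of-study SD only for placebo. A treated-arm end-of-study SD about 1.35–1.39 times baseline would bring NAD at 8.7 µM to 140. This makes the argument conditional, but the protocol states no such ratio, and its 128 for urine reproduces with equal SDs.

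**A reader might infer that 8.7 is a misprint for 7.7.** The 80%-detectable difference at 28 per arm is indeed 7.70 µM. But the noncentral-t route that reproduces 128 gives 144 at 7.7, and a different SD or a wrong total fits equally well. The documents do not decide between them.

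**A reader might also infer that the planned analysis is underpowered.** For NAD this needs both the unproven 7.7 µM (75% under ANCOVA with Tukey-Kramer) and a reading of section 8.3 that ignores its unadjusted coefficient rule. Pairing Tukey-Kramer with a change score gives 66% for urine and 73% for NAD at 8.7, but section 8.3 specifies ANCOVA on the visit value. Sizing on a simpler test than the final ANCOVA is common practice. What remains is narrower: the stated 80% is the power of neither reading of section 8.3 at the planned 140.

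**The figures concern erythrocytes.** The February 2019 note at the front of the protocol records that NAD was measured in whole blood instead. That limits the bearing of the NAD line on the data obtained; it does not repair the line.

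**Conclusion.** The concern holds as stated in the heading. On section 8.1's own inputs, 8.7 µM with SD 10.1 needs about 112–116 subjects, and 112 by either route that reproduces 128. NAD therefore needs fewer subjects than the primary endpoint, and the rationale for powering on NAD is reversed.

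The conclusion rests on two-sided testing and equal SDs across arms. One-sided testing moves NAD further from 140. Which of the effect, SD or total is wrong cannot be settled from the protocol. Nothing here shows the primary endpoint to be underpowered: its power at 140 is above 80% under every test that sections 8.1 and 8.3 describe, given r = 0.5 and 28 completers per arm.

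**What to change.** Check the source calculation and correct whichever of the NAD effect, SD or total is wrong. If 8.7 and 10.1 stand, replace 140 on that line with 112–116 (stating the rounding rule) and delete the claim that NAD needs the larger sample. No substitute effect or SD should be adopted only because it returns 140.

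Keep the planned 140, justified as covering the 128 for the primary endpoint. Restate the power it gives with 28 completers per arm, primary endpoint first, naming the test each figure belongs to: the change-score comparison as sized, and the ANCOVA with Tukey-Kramer or with the unadjusted coefficient, as tabulated above.

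The cost is a few reworded sentences in section 8.1. Enrolment, endpoints and analyses are unaffected.

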#### **8.2 Analysis Plan**

- The **Safety Population** will consist of all subjects who received any amount of either product, and on whom any post-randomization safety information is available.

Protocol 15NRHC: A randomized, double-blind, placebo controlled parallel study investigating the effects of Niagen™ (Nicotinamide Riboside) on Niagen™ metabolites in healthy adults

- The **Intent-to-Treat (ITT) Population** consists of all subjects who received either product, and on whom any post-randomization efficacy information is available.
- The **Per Protocol (PP) Population** "Per Protocol (PP) Population" consists of all subjects who consumed at least 80% of treatment or placebo doses do not have any major protocol violations and complete all study visits and procedures connected with measurement of the primary variable.

### 8.3 Analysis Plan

An effectiveness analysis based on the modified intent-to-treat population and an efficacy analysis based on the per protocol population will be performed. Variables will be tested for normality and log-normality. Log-normally distributed variables will be analyzed in the logarithmic domain. Non-normal variables will be analyzed by appropriate non-parametric tests.

All missing values in the intent-to-treat (effectiveness) analysis will be imputed with the most recent previously-available value (LOCF, or "last-observation-carried-forward" imputation). No imputation will be performed for missing values of safety variables.

For each numerical endpoint, a summary table will be prepared with a variety of summary statistics including mean, standard deviation, median, minimum value, and maximum value for each time point-treatment pairing. In order to account for any a priori differences between groups, the summary statistics of the changes from baseline will also be provided. For parameters requiring the logarithmic transformation, the summary statistics will be provided as non-transformed values. Mean values will be displayed as graphs, with a separate line for each product, and error bars indicating  $\pm 1$  SEM. Mean changes from baseline will be graphed similarly.

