There are numerous proof-of-concept *in vitro* and *in vivo* studies (Bogan & Brenner, 2008; Canto et al., 2012; Khan et al., 2014) that indicate that NR supplementation has beneficial biological effects. However, to date there are no published reports on the safety and bioavailability of NR treatment in humans. We recently conducted a randomized, double-blind, cross-over study to examine the pharmacokinetic effects of Niagen™ dosing in healthy adults ((14NBHC, 2015), unpublished findings). Niagen™ was found to be readily absorbed and exhibit a dose-dependent relationship in human serum and urine. In addition, Niagen™ was well tolerated and presented no toxicity within the acute time-points (1-24h) of the trial. The aim for this study is to investigate the long-term effects of Niagen™ supplementation on Niagen™ metabolite concentrations in blood, urine, and muscle of healthy subjects. Importantly, because urinary N-methylnicotinamide levels are considered the most reliable biomarker for niacin supplementation (Jacob et al., 1998;

Protocol 15NRHC: A randomized, double-blind, placebo controlled parallel study investigating the effects of Niagen™ (Nicotinamide Riboside) on Niagen™ metabolites in healthy adults

Institute of Medicine, 1998), urinary N-methylnicotinamide levels will used as the primary endpoint for assessing Niagen™ metabolism .

Protocol 15NRHC: A randomized, double-blind, placebo controlled parallel study investigating the effects of Niagen™ (Nicotinamide Riboside) on Niagen™ metabolites in healthy adults

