### **Primary outcome:**

The difference in urinary methylnicotinamide levels between placebo and Niagen™ (100mg, 300mg, and 1000mg) treated subjects after 8 weeks of supplementation.

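### Normality tests on the outcome variables choose the scale, and even the test, for the primary endpoint; the scale should be fixed in advance and residuals used only as a diagnostic

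*Protocol*

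**What the plan says.** Section 8.3 of the protocol sets a two-step rule. First: "Variables will be tested for normality and log-normality. Log-normally distributed variables will be analyzed in the logarithmic domain". Then: "Non-normal variables will be analyzed by appropriate non-parametric tests". Under the subheading on statistical tests, the default is ANCOVA on the visit value, with treatment group as factor and the Day 0 value as covariate. The fallback is named: "Numerical endpoints that are intractably non-normal will be assessed by the Mann-Whitney U test".

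The rule covers numerical efficacy endpoints without exception, so it includes the primary outcome in section 2: "The difference in urinary methylnicotinamide levels between placebo and Niagen™ (100mg, 300mg, and 1000mg) treated subjects after 8 weeks of supplementation". No scale is fixed for that endpoint and residuals are not mentioned. The normality test, its threshold, and whether it is run on pooled values or arm by arm are not given.

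The Introduction expects the arms to differ: in the earlier crossover study Niagen was found to "exhibit a dose-dependent relationship in human serum and urine". The doses here span a tenfold range.

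**The concern.** ANCOVA needs well-behaved residuals given arm and baseline. It does not need a normally distributed outcome. If four dose groups with different centres are pooled, the result is a mixture. It can fail a normality test on both the raw and the log scale even when every arm is exactly log-normal and log-scale ANCOVA is fully valid.

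The primary analysis would then be replaced because of the treatment effect itself. Mann-Whitney U compares two groups in a four-arm trial and makes no use of the Day 0 value. The ANCOVA coefficient and the Tukey-Kramer step in section 8.3 have no counterpart under it. At stake are a primary test settled only after the outcome data are seen, and some loss of power.

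**Working it through.** **The plan's own figure first.** Section 8.1 gives SD 3.1, difference 2.5, baseline correlation 0.5, power 80%, alpha 0.05 (two-sided reproduces the figure) and attrition 20%.
- SD of change: 3.1 × √(2 × (1 − 0.5)) = 3.1.
- n per arm: 2 × (1.960 + 0.842)² × 3.1² / 2.5² = 24.1, so 25.
- With attrition: 25 / 0.8 = 31.25, so 32. Times 4 arms = 128, as stated.

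With 35 randomised per arm and 20% attrition, 35 × 0.8 = 28 remain. That number is used below.

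**How often the rule leaves ANCOVA.** Assumptions, because the documents give none of these: exactly log-normal data, constant CV, dose ratios as listed, and Shapiro-Wilk at 0.05. From the protocol: 28 per arm and correlation 0.5. The table shows the share of simulated trials failing on both raw and log scales when values are pooled across arms.

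| Placebo:100:300:1000 mg | CV 0.3 | CV 0.5 | CV 0.7 |
|---|---|---|---|
| 1:1.5:2.5:5 | 77% | 16% | 6% |
| 1:1:1.5:5 | 100% | 91% | 40% |
| 1:1.3:1.7:2.5 | about 4-10% across the three CVs | | |

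Repeat runs move these by up to about 5 points (the 40% came out at 45% on repeat). Log-scale residuals from the same data pass in about 95% of trials throughout.

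**By-arm testing.** A shift between arms does no harm here. But if any failing arm counts, four 5% tests give 1 − 0.95⁴ = 18.5% failures on the log scale alone. The simulated rate of failing both scales is about 14-20%.

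**A second setting with the protocol's SD of 3.1** (normal errors, assumed baseline mean 10, pooled testing, 28 per arm). Failure of both scales is 4% if all doses shift by 2.5, 3% for shifts 0/2.5/5/7.5, 11% for 0/2.5/5/10, and 80% for 0/2.5/7.5/15. Testing residuals gives 3-6% throughout all settings tried.

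**Cost of the switch.** Take the smallest non-null ratio in the first two shapes, 1.5 (ln 1.5 = 0.405), with an unadjusted pairwise comparison at 28 per arm. The log SD is s = √ln(1 + CV²).
- ANCOVA: SE = s × √(1 − 0.5²) × √(2/28); power ≈ Φ(0.405/SE − 1.96).
- Mann-Whitney: SE = s × √(2/28) / √0.955, where 0.955 = 3/π is its efficiency for normal data.

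| CV | s | SE, ANCOVA | Power | SE, Mann-Whitney | Power |
|---|---|---|---|---|---|
| 0.3 | 0.294 | 0.068 | >99.9% | 0.080 | 99.9% |
| 0.5 | 0.472 | 0.109 | 96% | 0.129 | 88% |
| 0.7 | 0.632 | 0.146 | 79% | 0.173 | 65% |

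The approximation gives losses of 8 and 14 points at CV 0.5 and 0.7; simulation gives roughly 9-16. With SD 3.1 and difference 2.5, simulated power is about 92% for ANCOVA and 82% for Mann-Whitney.

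**Frequency times cost**, treating the two as independent and using the approximate losses:
- 1:1:1.5:5: 0.91 × 8 ≈ 7 points at CV 0.5; 0.40 × 14 ≈ 6 points at CV 0.7.
- 1:1.5:2.5:5: 0.16 × 8 ≈ 1 point; 0.06 × 14 ≈ 1 point.

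**The case against.** The strongest reply is that the mixture problem needs pooled testing, which the protocol nowhere states. A statistical analysis plan, not shown here, may settle the unit of testing, and the word intractably suggests a last resort rather than an automatic switch. This stands as a limit on the size of the effect. It does not remove the point: the protocol itself ties the choice to the variables, and by-arm testing also misroutes valid data. Counting only failures on both scales already allows for trying a transformation first.

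The large percentages also come from chosen shapes. At the planned 2.5 difference, or with modest evenly spaced shifts, switching stays near the nominal 5%. That is correct.

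Three stronger readings are tempting and are not supported.
- *The low dose loses precision on the raw scale.* With constant CV the pooled SD would be 1.5 to 2.3 times the SD relevant to 100 mg versus placebo. But in the log-normal settings above, pooled raw values passed the normality test in 0% of runs, so under pooled testing that analysis would not be carried out.
- *The stronger the effect, the weaker the analysis.* Where 1:1.5:2.5:5 switches most often (CV 0.3), power is near 100% either way.
- *The tables are wrong.* For log-transformed parameters "the summary statistics will be provided as non-transformed values". These are descriptive tables, openly labelled, which also give the median. Adding geometric means is a reporting preference.

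**Conclusion.** The point holds as a weakness in a written rule. Section 8.3 lets tests on outcome variables decide the scale and the test for the primary endpoint, and its fallback drops the baseline covariate.

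The size depends on assumptions that the documents do not supply: pooled or by-arm testing, Shapiro-Wilk at 0.05, the CV and the dose-response shape. Misrouting of valid data runs from near nominal to almost certain under pooled testing, and is about 14-20% by arm if any failing arm counts. The practical cost is concentrated where the top dose stands far apart and the CV is 0.5-0.7, above all 1:1:1.5:5. Elsewhere the switch is either rare or nearly free in power. The protocol's tenfold dose range and expected dose dependence make a separated top dose plausible, but do not establish it. This is a worthwhile, inexpensive correction and does not by itself put the trial's conclusion in doubt.

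**What to change.** Reword section 8.3 as follows.
- Fix the primary analysis in advance: ANCOVA on log creatinine-standardised urinary methylnicotinamide, with log Day 0 value as covariate and treatment group as factor.
- Report geometric mean ratios to placebo with 95% confidence intervals.
- Use model residuals as a diagnostic only, with no test-driven change of scale or method for the primary endpoint.
- Keep rank ANCOVA as a sensitivity analysis. Unlike Mann-Whitney U, it handles four arms and keeps the baseline covariate.

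The cost is a wording change, with no extra data or visits. Effects on this endpoint would be read as ratios rather than differences. The untransformed summaries can stay as descriptive tables.

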### **Secondary outcomes:**

1. The rate of increase in urinary methylnicotinamide levels between placebo- and NR (100mg, 300mg, and 1000mg)-treated subjects after 8 weeks.
2. The difference and rate of increase in other NR metabolites (see section 6.7) levels in blood between placebo- and NR (100mg, 300mg, and 1000mg)-treated subjects after 8 weeks.
3. The difference and rate of increase in other NR metabolites (see section 6.7) levels in urine between placebo- and NR (100mg, 300mg, and 1000mg)-treated subjects after 8 weeks.
4. The difference in other NR metabolites (see section 6.7) levels in muscle between placebo- and NR-(100mg, 300mg, and 1000mg)-treated subjects after 8 weeks

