### 3 STUDY DESIGN

[figure not shown]

This will be a randomized, double blind, placebo controlled, 4-arm parallel study that will investigate the effect of Niagen™ supplements in healthy subjects on Niagen™ metabolite concentrations in urine, blood, and muscle in healthy males and females.

The planned sample size for this study is 140 healthy males or females, with 35 subjects randomized equally to each of the four study arms in a double-blind manner at a ratio of 1:1:1:1.

| Study Arm      | Subject Number |
|----------------|----------------|
| Niagen™ 100mg  | N = 35         |
| Niagen™ 300mg  | N = 35         |
| Niagen™ 1000mg | N = 35         |
| Placebo        | N = 35         |
| Total   | N = 140 |

In order to evaluate primary, secondary, exploratory, and safety outcomes, study assessments will be conducted at baseline and all study visits. At each visit to the clinic, whole blood (which will be centrifuged and separated into WBC, RBC and plasma fractions) and urine will be collected from each participant for NR metabolite and creatinine analysis. REE will also be calculated at baseline and all subsequent clinic visits using indirect calorimetry. A muscle biopsy will be collected at baseline and end of study (week 8).

The study will be conducted at a single site in London, Ontario.

Protocol 15NRHC: A randomized, double-blind, placebo controlled parallel study investigating the effects of Niagen™ (Nicotinamide Riboside) on Niagen™ metabolites in healthy adults

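### LOCF in the ITT analysis enters the pre-dose biopsy as the Day 56 muscle result, shrinking the muscle effect by the share of missing biopsies; for urine and blood the direction of bias is unknown

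*Protocol*

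**What the plan says.** Section 8.3 of the protocol fixes the handling of missing efficacy data: "All missing values in the intent-to-treat (effectiveness) analysis will be imputed with the most recent previously-available value". The next sentence exempts safety variables. No efficacy variable is exempt.

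The sampling times differ by matrix. For muscle, section 3 says "A muscle biopsy will be collected at baseline and end of study (week 8"; section 6.7.3 and Appendix 1 agree that there are two biopsies and none between. Section 6.3 places the first before the first dose. Urine and blood are taken at Days 0, 7, 14, 28 and 56; section 3 says "study assessments will be conducted at baseline and all study visits".

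The outcomes affected are:
- Primary (section 8.1): "The primary efficacy endpoint is the change urinary methylnicotinamide levels from baseline to Day 56".
- Secondary outcome 1: "The rate of increase in urinary methylnicotinamide levels between placebo- and NR".
- Secondary outcome 4: "The difference in other NR metabolites (see section 6.7) levels in muscle between placebo- and NR-(100mg, 300mg, and 1000mg)-treated subjects after 8 weeks".

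Section 8.2 admits to the ITT set anyone who took product "and on whom any post-randomization efficacy information is available". One Day 7 urine value is therefore enough to enter, with or without a second biopsy. Under section 8.3 each visit value is analysed by ANCOVA with the Day 0 value as covariate. Section 8.1 plans "With an estimated 20% attrition over the course of this study".

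**The concern.** LOCF needs an earlier on-treatment observation to carry. For muscle there is none. The only earlier value is the untreated one, so the rule records zero change whatever the product did, and for these participants the outcome equals the covariate. On an active arm this pulls the estimate toward no effect; on placebo it adds nothing. A reader of the ITT muscle result would then see an effect smaller than the one the biopsies showed, for a reason unrelated to the product.

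For urine and blood the rule is less crude but still sets all change after the last visit to zero. That sits awkwardly with a Day 56 primary endpoint and with secondary outcomes about rate of increase. The rule is stated in the protocol, so this is not a detail left to an analysis plan that is not shown.

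**Working it through.** **Inputs.** From section 8.1: urine SD 3.1 and effect 2.5 µM/mM creatinine; erythrocyte NAD SD 10.1 and effect 8.7 µM; baseline to end-of-study correlation 0.5; attrition 20%. From section 3: 35 per arm. The protocol gives no SD or effect for muscle and no metabolite time course, so those are assumed where marked.

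**The plan's own figure.** SD of change = 3.1 × √(2 × (1 − 0.5)) = 3.1. With two-sided alpha 0.05 and 80% power, n per arm = 2 × (1.960 + 0.842)² × 3.1² / 2.5² = 24.1, so 25. Then 25 / 0.8 = 31.25, so 32, and 4 × 32 = 128, the stated urine total. The 20% is thus used as loss of measured participants: 0.20 × 35 = 7 per arm at the planned size.

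**Muscle.** Let m be the share of ITT participants without a Day 56 biopsy, equal across arms and unrelated to outcome. Observed participants contribute the true difference δ; imputed ones contribute 0, since baselines are balanced by randomization. Expected difference = (1 − m) × δ.

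- m = 10%: 0.90 δ
- m = 20%: 0.80 δ

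The factor does not depend on δ or the SD. On the log scale that section 8.3 allows, it applies to the log difference. Borrowing the NAD and urine inputs as illustration, ANCOVA simulation (35 per arm, correlation 0.5, 4,000 runs) gave:

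| Missing per arm | True effect | (1 − m) × δ | LOCF, simulated | Observed only, simulated |
|---|---|---|---|---|
| 4 of 35 | 8.7 | 8.7 × 31/35 = 7.71 | 7.72 | 8.71 |
| 4 of 35 | 2.5 | 2.5 × 31/35 = 2.21 | 2.22 | 2.50 |
| 7 of 35 | 8.7 | 8.7 × 28/35 = 6.96 | 6.94 | 8.67 |
| 7 of 35 | 2.5 | 2.5 × 28/35 = 2.00 | 1.98 | 2.48 |

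(10% of 35 is 3.5, simulated as 4.)

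**Power and type I error for muscle.** Assume a 0.6 SD effect with 7 of 35 missing (8,000 runs). LOCF: expected estimate 0.80 × 0.6 = 0.48 SD, standard error 0.196, ratio 2.45, power about 68%. Participants with both biopsies: 0.60 SD, standard error 0.232, ratio 2.59, power about 72%. With no true effect, LOCF rejects about 5% of the time at 10%, 20% and 30% missing. The smaller LOCF standard error therefore produces no false positives here; it describes a shrunken estimate.

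**Urine and blood.** Let f be the carried effect as a fraction of the Day 56 effect. Expected difference = δ × [(1 − m) + m × f]. With δ = 2.5, m = 20% and f assumed:

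| f | Meaning | Expected | Simulated |
|---|---|---|---|
| 0.5 | still rising | 2.5 × (0.8 + 0.10) = 2.25 | 2.26 |
| 0.75 | still rising | 2.5 × (0.8 + 0.15) = 2.375 | 2.40 |
| 1.0 | plateau already reached | 2.5 × (0.8 + 0.20) = 2.50 | 2.49 |
| 1.2 | early peak | 2.5 × (0.8 + 0.24) = 2.60 | 2.60 |

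The sign depends on f, which the protocol does not supply.

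**The case against.** The strongest reply has four parts.

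- **The missing share is probably below 20%.** Section 4.4 asks for end-of-treatment evaluations at withdrawal where possible, which may include a biopsy. Section 7.2.2 keeps some participants attending after they stop product. Anyone who leaves before giving a post-randomization efficacy value is outside the ITT set. This stands: 20% is an upper illustration. It does not remove the problem, because none of these provisions yields a biopsy from someone lost to follow-up or unwilling to have a second one. The protocol gives no refusal rate, so nothing can be added to the 20% on that account.
- **The per-protocol analysis is not subject to LOCF.** True, since the rule is stated only for the ITT analysis. But that set is limited to compliant participants without major violations and requires completion of the primary-variable procedures, not of the biopsy. It does not correct the ITT muscle estimate.
- **The harm is modest and conservative.** Also true: type I error holds, about four points of power are lost in the assumed case, and muscle is a secondary outcome without its own power calculation. An avoidable bias in the estimate remains.
- **No bias is shown for urine or blood.** This stands. A reader might infer that LOCF pulls the primary urine effect toward zero, because secondary outcome 1 speaks of a rate of increase. Naming that outcome is not evidence that levels keep rising to Day 56. A figure such as a 14% loss (2.5 to about 2.15) needs an assumed linear rise and dropout spread evenly after Days 7, 14 and 28: mean f = (0.125 + 0.25 + 0.50)/3 = 0.29, and 2.5 × (0.8 + 0.2 × 0.29) = 2.15. The protocol supports neither assumption.

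**Conclusion.** The point holds for muscle. As written, the ITT analysis of secondary outcome 4 is biased toward zero by the fraction of missing second biopsies: about 10% of the effect at 10% missing and 20% at 20%, given equal missingness across arms that is unrelated to outcome. A biopsy obtained at early withdrawal would lower the missing share, although it is still not an 8-week value.

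For urine and blood, including the primary endpoint, the conclusion is narrower. LOCF fixes later change at zero and treats one carried value as observed, with bias of unknown direction: nil after an early plateau, toward zero if levels are still rising, away from zero after an early peak or where on-treatment values are carried for people who stopped product. The document does not support saying that the primary result is diluted.

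This should be fixed, but it does not by itself undermine the primary analysis.

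**What to change.** Amend section 8.3 as follows.

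1. **Muscle:** impute nothing. Analyse Day 56 muscle values by ANCOVA with the Day 0 value as covariate, in ITT participants with both biopsies, and report the number missing by arm.
2. **Urine and blood (preferred):** replace LOCF with a mixed model for repeated measures over Days 7, 14, 28 and 56, with baseline, treatment, visit and treatment-by-visit terms. Take the Day 56 contrasts from it. The same model can supply the contrasts for rate of increase. Keep LOCF as a sensitivity analysis.

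The cost is a few sentences and slightly more programming; no visit or sample changes. Each replacement has its own assumption. The repeated-measures model takes data to be missing at random. The muscle ANCOVA takes a missing biopsy to be unrelated to the Day 56 value, given arm and baseline. Both should be stated in the plan.
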